#### 4) Supplemental report

After receiving a secondary report or supplemental report from the Principal Investigator, the Study Representative Physician/Study Secretariat will append the additional information from the primary report and the opinion based thereon to a “Report on Diseases, etc.” to be delivered to the Certified Clinical Research Review Board as defined under the Clinical Research Act Enforcement Regulations, and this secondary report or supplemental report will be reported to the Local (Branch) Health and Welfare Bureau, and the Medical Economics Division, Health Insurance Bureau, of the Ministry of Health, Labour and Welfare in the same manner as was done with the primary report.

#### 10.3.3. Notification to the Principal Investigator of each facility

When the Study Representative Physician/Study Secretariat reports to the Certified Clinical Research Review Board, the Principal Investigators of all participating research facilities will be notified in a document (by email) of the details of the review and recommendation. In addition, if there is an urgent need to be informed of the details, the Study Representative Physician/Study Secretariat will notify the Principal Investigators without waiting for the review by the Certified Clinical Research Review Board. Moreover, when a report is made to the Minister of Health, Labour and Welfare, the Study Representative Physician/Study Secretariat will notify the Principal Investigators of all participating research facilities of this subject matter.

If a report has not been made to the Certified Clinical Research Review Board or the Minister of Health, Labour and Welfare, the Principal Investigator of the facility making the report will be notified in a document (by email) of the determination of the Study Representative Physician/Study Secretariat.

#### 10.4. Response to the Principal Investigator of participating facilities (including the relevant facility)

When an adverse event is the subject of a “Report on Diseases, etc.” to the Certified Clinical Research Review Board, the Principal Investigator from the facility participating in this research will report to the Study Center Director according to instructions from the Study Representative Physician/Study Secretariat as per the regulations of the corresponding medical institution.

#### 10.5. Response to the Efficacy and Safety Evaluation Committee

When an adverse event is the subject of an urgent report, the Study Representative Physician/Study Secretariat is to determine whether or not the trial is to be continued, and contacts the Efficacy and Safety Evaluation Committee to request an examination to determine whether or not to continue the trial.

#### 10.6. Reports on pregnancy and overdose

If the patient or partner of the patient is found to be pregnant, or if an overdose of study drug is identified, the principal investigator (or the co-investigator from whom instruction was received) will contact the Coordination Office immediately after obtaining the information. Even if no adverse events are present, the report on pregnancy and overdose should be completed as specified in the “Procedure for Handling

Safety Information” and submitted to the Coordination Office. The Coordination Office will also share information with study drug providers as appropriate.

“Overdose” refers to a case where the dose administered exceeds the dose specified in the package insert by 10%.

## 10.7. Safety information reports to the company providing the medication

According to the details of the contract, the co-investigator/principal investigator or the Study Representative Physician/Study Secretariat will report adverse event information to the department in charge at the pharmaceutical company that handles the relevant medication (by email, fax, etc.).

## 11. Efficacy assessments

When any treatment is registered in this study, the tumor response effect assessment will be done according to procedures in “The New Guidelines for the Response Evaluation Criteria In Solid Tumors (RECIST guidelines) revised version 1.1 (JCOG Japanese translation revised version 1.1)”(15).

Although the determination interval of overall efficacy is not determined, a comprehensive evaluation is always performed 16±1 weeks after the start of treatment. Furthermore, in this study, we do not collect the details of the efficacy assessments, but collect in the eCRF only the results of the best overall efficacy (11.1.10.) that were confirmed in each treatment.

### 11.1. Efficacy assessments

#### 11.1.1. Baseline evaluation

In accordance with “8.1. Pre-registration evaluation items,” specifics of the neoplastic lesions are identified before enrollment with head, chest, abdomen, and pelvis contrast CT imaging (slice thickness ≤ 5 mm; MRI is also acceptable for head scans), with each lesion classified as a “measurable lesion” or “non-measurable lesion.”

The tumor diameter measurement is performed on the cross-sectional image of the CT or MRI scan, and measurements from sagittal or coronary sections from the three-dimensional image reconstruction are not used. The baseline assessment is performed using the most recent imaging exam within 28 days prior to enrollment. If the imaging exam is redone after enrollment and before the treatment starts, the most recent imaging exam results are to be used.

#### 11.1.2. Definition of measurable lesion

Measurable lesions are those that fall under any of the following.

- [1] Lesion other than a lymph node lesion (non-lymph node lesion) with a maximum diameter of ≥ 10 mm by CT or MRI
- [2] Lymph node lesion with a short diameter ≥ 15 mm by CT (a lymph node lesion with a short diameter of ≥ 10 mm and < 15 mm is a non-target lesion, and a lymph node with short diameter of < 10 mm is not a lesion)

Any lesions other than those described above are non-measurable lesions.

Be aware that the following lesions are non-measurable lesions regardless of the examination method or the size of the lesion.

- Bone lesions (except osteolytic bone metastases with measurable soft tissue components)
- Cystic lesions (except metastatic cystic lesions when there are no other measurable non-cystic lesions)
- Lesions with a history of local treatment such as radiotherapy
- Pial meningeal lesion
- Ascites, pleural effusion, pericardial effusion
- Lymphangiopathy of the skin and lungs
- Abdominal masses and enlargements of abdominal organs that are palpable but not measurable by imaging methods

### 11.1.3. Selection of target lesion(s) and baseline recording

Among the measurable lesions observed at the time of enrollment, up to 5 target lesions are selected (2 per organ\*) in descending order of diameter (long diameter for non-lymph node lesions and short diameter for lymph node lesions). During this process, selections are made taking into consideration that organs having measurable lesions should be included as uniformly as possible and with a focus on reproducible repeated measurements (avoid lesions that are difficult to measure even if the diameter is large).

For the selected target lesions, describe in the chart the lesion site (code), examination method, examination date, long diameter of non-lymph node target lesions, short diameter of lymph node target lesions in order from head to foot, along with the sum of the diameters of all target lesions (hereinafter, "lesion diameter sum").

\* How to count organs

Organize all the left and right organs (lung, kidney, etc.) as a single organ

All lymph nodes are one organ each regardless of site

### 11.1.4. Baseline recording of non-target lesions

Lesions that were not selected as target lesions, whether or not measurable, are all recorded as non-target lesions, and the lesion site, examination method, and examination date are recorded in the chart. Multiple non-targeted lesions within the same organ can be recorded as one lesion (e.g., multiple enlarged pelvic nodes, multiple liver metastases).

### 11.1.5. Tumor response evaluation

16±1 weeks after the start of treatment and at the time of treatment discontinuation, and regardless of whether or not treatment will be prolonged, an evaluation of the target lesions and non-target lesions is to be made according to "8.2. Tests and evaluations during the protocol treatment period" in the same manner as during enrollment, and the diameters of the target lesions and any disappearance or exacerbation of non-target lesions are to be recorded in the chart.

Even if the overall efficacy is determined to be "PD," the protocol treatment is not to be discontinued if it is determined that continuation of the protocol treatment is clinically appropriate, and to continue the protocol treatment even after the overall efficacy is determined as PD, the efficacy determination during this period should be performed according to the following.

### 11.1.6. Criteria for determining efficacy on the target lesions

- **Complete Response (CR):**  
All non-lymph node target lesions have disappeared and all lymph node target lesions have a small diameter < 10 mm.  
If a lymph node target lesion is selected at baseline, the efficacy on the target lesion can be CR even if the lesion diameter sum is not 0 mm.
- **Partial Response (PR):**  
Reduction of 30% or more in the target lesion diameter sum compared to baseline
- **Progressive Disease (PD):**  
An increase of 20% or more in the target lesion diameter sum compared to the smallest lesion diameter sum over the course (when the minimum value occurs at baseline, that will be the smallest lesion diameter sum over the course), and an increase in absolute value of the lesion diameter sum by  $\geq 5$  mm
- **Stable Disease (SD):**  
There is no decrease corresponding to PR and no increase corresponding to PD
- **Not all Evaluated (NE):**  
If an examination cannot be performed for any reason, or if it cannot be judged as CR, PR, PD, or SD

$$\text{Sum reduction ratio} = \frac{(\text{Pre-treatment sum}) - (\text{Sum at evaluation})}{(\text{Pre-treatment sum})} \times 100\%$$

$$\text{Sum increase ratio} = \frac{(\text{Sum at evaluation}) - (\text{Minimum sum})}{(\text{Minimum sum})} \times 100\%$$

- ① The measured value is to be recorded as long as the diameter of the target lesion can be measured (for example, < 5 mm), but if it is determined that the diameter of the target lesion is "too small to measure" regardless of the CT slice thickness, the determination is that the tumor lesion does not remain when the diameter is 0 mm, and that the tumor does remain when the diameter is 5 mm.
- ② If the reduction ratio satisfies the condition for PR and at the same time the increase ratio satisfies the condition for PD, PD is assumed.
- ③ If one lesion separates during treatment, add the diameter of each to the diameter sum.
- ④ If multiple lesions coalesce during treatment and the border cannot be identified, the diameter of the coalesced lesion is added to the lesion diameter sum. Even if the lesions are in contact with each other, the diameter of each lesion is added to the lesion diameter sum if the lesion boundaries can be identified.

#### 11.1.7. Criteria for determining efficacy on the non-target lesions

- **Complete Response (CR):**  
All non-lymph node non-target lesions have disappeared and all lymph node non-target lesions have a small diameter < 10 mm.
- **Non-CR/non-PD:**  
When one or more non-target lesions remain (including remaining lymph node non-target lesions with a small diameter of ≥ 10 mm)
- **Progressive Disease (PD):**  
"Apparent exacerbation" of existing non-target lesions (including recurrences).  
In the case of measurable lesions: even if the efficacy on the target lesion is SD or PR, and an increase in the overall tumor volume is determined as an "apparent exacerbation" based on changes in non-target lesions, a significant exacerbation of non-target lesions should be observed to a sufficient degree to discontinue treatment. When the efficacy on the target lesion is SD or PR, an increase in the tumor volume of the non-target lesions that is far more than the decrease of the tumor volume is regarded as "apparent exacerbation"; otherwise it is Non-CR/non-PD.  
In the case of having only non-measurable lesions: an indication of "apparent exacerbation" is when an increase in non-target lesions is judged to clearly exceed a tumor volume equivalent to a 20% increase in diameter or a 73% increase in tumor volume
- **Not all Evaluated (NE):**  
If an examination cannot be performed for any reason, or if it cannot be determined as CR, PR, PD, or SD

#### 11.1.8. Appearance of new lesions

If a lesion not present at baseline is observed after the start of treatment, it is considered as the appearance of a "new lesion."

However, qualifying as a "new lesion" requires that it cannot be a change in the image due to the difference in imaging method from the examination performed during the baseline evaluation or a change in image modality, or a change on the image due to a pathological condition other than a tumor. For example, a cystic lesion formed within a lesion due to necrosis of a liver metastasis is not a new lesion. Lesions newly identified by examination of sites not required at baseline (pre-enrollment evaluation) are considered new lesions. The diameter of the new lesion (maximum diameter of non-lymph node lesions,

short diameter of lymph node lesions) is not added to the lesion diameter sum.

If one lesion disappears and then later reappears, the measurement is continued without making it a “new lesion.” However, the efficacy at the time when the lesion reappears differs depending on the condition of other lesions. When a lesion reappears after CR, the overall efficacy is determined to be PD at the time of reappearance. On the other hand, if a lesion that has once disappeared then reappears when the overall efficacy is PR or SD, the diameter of that lesion will be added to the diameter sum of the remaining lesions to calculate the efficacy. That is, in a state in which many lesions remain, even if one lesion apparently reappears after “disappearing,” this alone does not make a determination of PD, and it is when the sum of all the lesion diameters meets the PD criterion that the case is determined as PD. This is because there is recognition that most lesions do not truly “disappear” but are only delineated by the resolution limitations of the imaging modality used.

When there is a possibility that the lesion is a new lesion but cannot be confirmed, it is not considered a new lesion, and it will continue to be evaluated at the next imaging examination. When it is confirmed that the lesion is a new lesion from re-examination of the image exam results, the appearance of the new lesion is defined as the date of the image examination when the new lesion was confirmed.

### 11.1.9. Overall response

The overall response is determined according to Table 11.1.9a below based on the combination of the efficacy on the target lesions, the efficacy on the non-target lesions, and whether or not any new lesions have appeared. The overall response in the absence of target lesions at baseline is determined according to Table 11.1.9b according to the efficacy on non-target lesions, and whether or not any new lesions have appeared.

Table 11.1.9a Overall response at each time point: when target lesions are present (doesn't depend on whether or not non-target lesions are present)

| Target lesion | Non-target lesion | New lesion | Overall efficacy |
|---------------|-------------------|------------|------------------|
| CR            | CR                | No         | CR               |
| CR            | Non-CR/non-PD     | No         | PR               |
| CR            | NE                | No         | PR               |
| PR            | Non-PD or NE      | No         | PR               |
| SD            | Non-PD or NE      | No         | SD               |
| NE            | Non-PD            | No         | NE               |
| PD            | Any               | Yes or no  | PD               |
| Any           | PD                | Yes or no  | PD               |
| Any           | Any               | Yes        | PD               |

Table 11.1.9b Overall response at each time point: when only non-target lesions are present

| Non-target lesion    | New lesion | Overall efficacy |
|----------------------|------------|------------------|
| CR                   | No         | CR               |
| Non-CR/non-PD        | No         | Non-CR/non-PD    |
| Defective evaluation | No         | NE               |
| PD (clear worsening) | Yes or no  | PD               |
| Any                  | Yes        | PD               |

### 11.1.10. Best Overall Response

The overall response is “good” in the order of CR > PR > SD > PD > NE, and the best overall response is determined according to the following criteria. When it corresponds to the definitions of multiple classifications, it is classified as the better one in the order of CR > PR > SD > PD > NE. However, when there are no target lesions at baseline, the best overall response does not use PR, and uses non-CR/non-PD instead of SD.

- **Complete Response (CR):**

When an overall response of CR is obtained two or more times continuously at intervals of 4 weeks (28 days) or more.

Furthermore, the day when the second overall response of CR is confirmed and the best overall effect of CR is determined is the day of confirmed CR.

- **Partial Response (PR):**

When an overall response of PR or better (CR or PR) is obtained two or more times continuously at intervals of 4 weeks (28 days) or more.

Furthermore, the day when the second overall response of PR is confirmed and the best overall effect of PR is determined is the day of confirmed PR.

- **Stable Disease (SD):**

In the case where neither CR nor PR is obtained as the best overall response, and there is at least one overall response of SD or better.

However, the shortest period of SD is 6 weeks from the start of protocol treatment.

- **Progressive Disease (PD):**

When the overall response is PD without corresponding to a best overall response of either CR, PR, or SD.

- **Not Evaluable (NE):**

When all of the overall responses are NE.

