### 6.2.2. Criteria for discontinuing the protocol treatment

The protocol treatment should be discontinued if any of the following is true.

- 1) When it is determined that the protocol treatment is ineffective according to any of the following
  - ① If a marked increase in the lesion was observed after starting treatment, and it was determined necessary to change treatment.  
If it is determined that continuing the protocol treatment is clinically appropriate even if it is determined as “progressive disease” (PD) by the response evaluation from imaging, the protocol treatment is continued and not discontinued.
  - ② If a deterioration of clinical symptoms determined to be due to disease progression is observed
- 2) If the protocol treatment cannot be continued due to an adverse event
  - ① When a Grade 4 adverse event is observed (except for the following events)
    - Hematologic toxicity: anemia, hypocellular marrow, lymphocyte count decrease, neutrophil count decrease, leukocytopenia, platelet count decrease, or CD4 lymphocytopenia according to the “Japanese translation JCOG version of the NCI Common Terminology Criteria for Adverse Events v 5.0 (CTCAE v5.0)” (hereinafter, CTCAE v5.0-JCOG) (13)
    - Non-hematologic toxicity: Alkaline phosphatase increase, GGT increase, high cholesterol, hypertriglyceridemia, hyperuricemia, and transient electrolyte abnormality according to the CTCAE v5.0-JCOG

For an adverse event which was not related to the protocol treatment, if the event was improved or recovered and the restarting the protocol treatment was considered to be profit for the patients, the Principal Investigator or the Co-investigator can discuss the restarting with the Study Representative/Study Secretariat.
  - ② If it was determined that the Principal Investigator or Co-investigator would need to discontinue the protocol treatment due to an adverse event that does not fall under [1] above
- 3) If the patient requests that the protocol treatment be discontinued because an association with the adverse event cannot be ruled out
  - Use this classification if the association with the adverse event cannot be denied
- 4) If the patient requests that the protocol treatment be discontinued because of the reason(s) that an association with the adverse event cannot be ruled out
  - ① In case of refusal by the patient before starting protocol treatment after enrollment

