### **6.3. Post-treatment**

In the present study, the post-treatment after discontinuing the protocol treatment is not particularly defined, but the following post-treatment can be assumed.

1. Participation in patient-proposed healthcare services for medications for other different genetic mutations obtained from the initially submitted specimens
2. Participation in patient-proposed healthcare services for the same type of medication for the same genetic abnormalities
3. Conducting some form of chemotherapy for practical diagnosis and treatment
4. Participation in other clinical trials and studies
5. Follow-up observation/best supportive care, etc.

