## 12.2. Definition of the endpoints

### 12.2.1. Primary endpoint

The primary endpoint is the response rate based on the best overall effect up to 16±1 weeks after the start of treatment among patients with measurable lesions in the FAS for each drug cohort. Subjects who do not achieve CR/PR by 17 weeks after the start of treatment, and if CR or PR is confirmed for the first time thereafter, are not included in the primary endpoint numerator.

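### Best overall response has no cut-off at progression, so a patient with PD followed by two PR assessments on continued treatment counts as a primary-endpoint responder

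*Protocol*

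**What the plan says.** Section 11.1.10 defines best overall response by ranking. When several categories apply, "it is classified as the better one in the order of CR > PR > SD > PD > NE". PR is given "When an overall response of PR or better (CR or PR) is obtained two or more times continuously" at intervals of at least 28 days, with no condition that the two assessments come before any PD. SD needs one assessment of SD or better, with a minimum of 6 weeks from the start of treatment. PD is what remains: "When the overall response is PD without corresponding to a best overall response of either CR, PR, or SD".

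Section 6.2.2 provides that, where imaging shows PD but continuing is judged clinically appropriate, "the protocol treatment is continued and not discontinued". Section 11.1.5 repeats this and adds that "the efficacy determination during this period should be performed according to the following", which leads into 11.1.6 to 11.1.10.

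Section 12.2.1 limits the primary endpoint only by time: "Subjects who do not achieve CR/PR by 17 weeks after the start of treatment" and respond later are left out of the numerator. Section 12.2.2 counts a patient as controlled if the best overall response is neither PD nor NE. For PFS it makes PD under the efficacy criteria an event on the imaging date, even when the clinical view is that the disease has not worsened.

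Section 11 says that the eCRF holds only the best overall result for each treatment, not the individual assessments. Section 2.3.6 rules out central review.

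**The concern.** The primary response rate drives the decision for each drug cohort: the 60% rule in 12.3.1 and the limits in Table 12.4. Under the present wording an imaging PD does not close the response assessment, so a later response on continued treatment replaces it. The same scan is then decisive for PFS and disregarded for response, and nothing in the protocol says that this is intended.

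Compared with a rule that stops at first PD, the present rule can only add responders. That makes the efficacy limit easier to reach and the inefficacy limit harder to reach, and 12.4 and 12.6 present the latter as an ethical safeguard.

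The gap cannot readily be closed at the analysis stage. Each site applies 11.1.10 and submits one category. An exacerbation date is collected (8.5, 8.6), but the assessments needed to work out the best response before that date are not.

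**Working it through.** **1. The plan's own limits.** Inputs: prior Beta(0.6, 1.4), thresholds 20% and 60%, probability limits 5% and 95% (12.3.1, 12.4). With x responders among n patients the posterior is Beta(0.6 + x, 1.4 + n − x). At n = 50:

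| x | Posterior | Probability |
|---|---|---|
| 37 | Beta(37.6, 14.4) | P(rate > 60%) = 0.971 |
| 36 | Beta(36.6, 15.4) | P(rate > 60%) = 0.944 |
| 5 | Beta(5.6, 46.4) | P(rate > 20%) = 0.029 |
| 6 | Beta(6.6, 45.4) | P(rate > 20%) = 0.069 |

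The limits are therefore 37 or more for efficacy and 5 or fewer for inefficacy, as in Table 12.4. All 18 rows checked between n = 7 and n = 60 agree with the table.

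**2. A path through the response rules (11.1.6, 11.1.9, 11.1.10).** Illustrative sums of target-lesion diameters, with no new lesion and no non-target PD:

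| Week | Sum (mm) | Change | Overall response |
|---|---|---|---|
| 0 | 100 | baseline | – |
| 6 | 125 | +25% and +25 mm on the minimum | PD |
| 12 | 65 | 35% below baseline | PR |
| 16 | 60 | 40% below baseline | PR |

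Weeks 12 and 16 are 28 days apart, so PR is met by week 17. PR outranks PD, and the patient enters the primary numerator. For PFS the patient has an event at week 6. The provision in 11.1.6 that PD prevails over PR applies only when both are met at the same assessment.

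**3. Disease control.** Take sums of 100, 125 at week 6 (PD) and 110 at week 12. The last is (110 − 100)/100 = 10% above the minimum, hence SD. One such assessment at 6 weeks or later is enough, so the patient counts as controlled after progression.

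**4. Possible size.** The protocol gives no rate of response after PD. Assume that 1 or 2 patients in 50 (2 or 4 percentage points) are added to the count. Exact binomial probabilities are:

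| Added responders | P(37 or more of 50), true rate 60% | P(5 or fewer of 50), true rate 10% |
|---|---|---|
| none | 0.028 | 0.616 |
| 2 points | 0.052 | 0.435 |
| 4 points | 0.090 | 0.281 |

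At a true rate of 60%, 2 points means 2/40 = 5% of non-responders, and 4 points means 4/40 = 10%.

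**The case against.** **A choice of what to estimate.** The protocol does not treat imaging PD as failure of the drug. It foresees treatment and scoring beyond PD, a response on continued study drug is still a response on that drug, and PFS and best response measure different things. This has force: counting such responses would be defensible if it were declared. It is not declared. The result follows from a ranking rule that never mentions the order of events.

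**A narrow path.** It takes three scans by about week 17, while only the scan at 16±1 weeks is mandatory (8.3.2). A new lesion that persists keeps the patient at PD (Table 11.1.9a). With the minimum at baseline, the sum must fall from at least 120% to at most 70% of baseline, a drop of 50/120, or about 42%, and hold for 28 days. All of this stands, and it makes the number affected small.

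**Little rests on one patient.** Any misclassification can matter at a limit, the study is not meant to test preset hypotheses (12.3.1), and crossing an interim limit only prompts consideration of stopping (12.4). This also stands, and it limits the weight of the point.

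**SAP or RECIST 1.1 may settle it.** Neither can be consulted here. But the protocol writes out its own rule, sites score by it, and an SAP would not have the individual assessments needed to correct it.

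**A stronger reading.** A reader might infer that responses after a switch to another drug are credited to the first drug, even twice when a patient joins a second cohort. Section 6.3 does foresee "Participation in patient-proposed healthcare services for medications for other different genetic mutations obtained from the initially submitted specimens", and 11.1.5 asks for the evaluation "regardless of whether or not treatment will be prolonged". The documents do not support that inference. Section 11 ties the recorded response to each treatment, and the calendar in 8.6 has no tumor evaluation after treatment is completed. The phrase in 11.1.5 may refer to delayed dosing, since 6.1.1 uses prolongation in that sense and 11.1.5 names discontinuation separately. Re-enrollment (2.7) requires new consent, and eligibility criterion 4 and 11.1.1 require imaging within 28 days before enrollment as the baseline. No text scores the second drug against the first drug's baseline. The switch is an ambiguity worth closing, and double credit is not shown.

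**Conclusion.** The point holds for progression on continued protocol treatment. Sections 6.2.2, 11.1.5, 11.1.10 and 12.2.1 together make a PD–PR–PR sequence by week 17 a primary response, and PD followed by SD at 6 weeks or later disease control, while 12.2.2 makes the same patient a PFS event at the date of PD.

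The number affected is probably small and is not documented. The calculations with 2 and 4 added points rest on an assumed range and do not forecast the bias. What does not depend on that range is the direction, upward only for the response rate, and the fact that one patient can decide a cohort: 36 against 37 of 50 for efficacy, 5 against 6 of 50 for inefficacy. The correction is worth making because it is cheap and because the data collected would not allow it later.

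**What to change.** State in 11.1.10 and 12.2.1 that best overall response uses only assessments up to the first overall response of PD or the start of any other anticancer treatment, whichever is first. List responses seen after PD on continued treatment separately, as descriptive. If the intention is to credit such responses in the primary endpoint, the protocol should say so and report how many there are.

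The cost is one sentence in each section, an eCRF item for a response after PD, and two dates. The exacerbation date is already collected. The start of subsequent treatment already bounds the adverse-event window in 8.3.1, so sites have to know it. For patients already scored, sites could be asked to check any recorded CR or PR where the exacerbation date falls within 17 weeks of the start of treatment.

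The downside is small: a genuine late response after an early apparent PD leaves the primary numerator and appears only in the listing. The change concerns scoring alone and leaves the decision to continue or stop treatment as it is.
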